## Abstract

**Background:**

Growing attention is given to the effects of health promotion programs targeting physical activity and healthy eating in individuals with mental disorders. The design of evaluation studies of public health interventions poses several problems and the current literature appears to provide only limited evidence on the effectiveness of such programs. The aim of the study is to examine the effectiveness and cost-effectiveness of a health promotion intervention targeting physical activity and healthy eating in individuals with mental disorders living in sheltered housing. In this paper, the design of the study and baseline findings are described.

**Methods/design:**

The design consists of a cluster preference randomized controlled trial. All sheltered housing organisations in the Flanders region (Belgium) were asked if they were interested to participate in the study and if they were having a preference to serve as intervention or control group. Those without a preference were randomly assigned to the intervention or control group. Individuals in the intervention group receive a 10-week health promotion intervention above their treatment as usual. Outcome assessments occur at baseline, at 10 and at 36 weeks. The primary outcomes include body weight, Body Mass Index, waist circumference, and fat mass. Secondary outcomes consist of physical activity levels, eating habits, health-related quality of life and psychiatric symptom severity. Cost-effectiveness of the intervention will be examined by calculating the Cost-Effectiveness ratio and through economic modeling.Twenty-five sheltered housing organisations agreed to participate. On the individual level 324 patients were willing to participate, including 225 individuals in the intervention group and 99 individuals in the control group. At baseline, no statistical significant differences between the two groups were found for the primary outcome variables.

**Discussion:**

This is the first trial evaluating both the effectiveness and cost-effectiveness of a health promotion intervention targeting physical activity and healthy eating in mental health care using a cluster preference randomized controlled design. The baseline characteristics already demonstrate the unhealthy condition of the study population.

**Trial registration:**

This study is registered at clinicaltrials.gov – NCT 01336946

## Background

People with mental disorders (MD) are at increased risk for overweight (Body Mass Index 25–29 kg/m²) and obesity (Body Mass Index >30 kg/m²) compared with the general population [1,2]. Beside the side effects of especially atypical antipsychotics on body weight [3], the higher prevalence of these conditions is associated with more sedentary lifestyles, which include less mild or strenuous forms of physical activity (PA) [4,5], and poorer dietary choices compared with the general population [6,7].

Growing attention is given to the effects of lifestyle interventions targeting PA and healthy eating in mental health care. The importance of health promotion in mental health care is acknowledged by the European Psychiatric Association declaring that maintaining a healthy body weight and shape by healthy eating and regular PA is a key component in order to reduce the risk of some important somatic diseases and to improve the overall health and well-being of patients [8]. However, the current literature on weight reduction interventions in mental health care appears to provide only limited evidence on the effectiveness of either psycho-educational programs or programs combining educational and exercise components [9].

Most attention of health economic research goes to health economic evaluations of medicines and technologies. Recently, more emphasis is given to health economic evaluations of preventive health care. In general populations, these kind of studies yield no conclusive evidence [10,11], which is probably explained by wide differences in program contents. In mental health care, the cost-effectiveness of health promotion interventions targeting PA and healthy eating has thus far not been investigated [12]. Consequently, the study of both the effectiveness and cost-effectiveness of health promotion interventions targeting PA and eating habits in mental health care is required to determine and compare the efficiency of these kinds of interventions.

The design of evaluation studies of public health interventions, like health promotion interventions, poses several problems and they require multiple, flexible, and community driven strategies [13].

In most clinical trials, participants are randomized as individuals to intervention or control groups. However, when individual randomization is not possible or desirable, groups of individuals can be randomized to intervention or control groups [14]. This kind of design is known as a cluster or group or community randomized trial [15]. According to the British Medical Research Council [16] a cluster randomized design has to be considered when the intervention is designed to be delivered to groups rather than to individuals. Cluster randomization may also be appropriate when there is a risk of contamination, i.e. when individuals randomized to the intervention group may influence others within the group [15].

Another concern in studies evaluating behavioral or psychosocial interventions is that the participants are typically informed about their experimental assignment soon after randomization. Being assigned to a non-preferred intervention condition could be disappointing, or even demoralizing and reduce participants’ interest to participate so that they may withdraw from the study [17,18]. An alternative design for the randomized controlled trial is the ‘patient preference design’, in which subjects are allowed to select the intervention assignment. Preference designs are useful when strong preferences among potential participants threaten either the ability to recruit an adequate sample size of representative participants or when such preferences threaten participants’ acceptance of treatment assignment, adherence, or retention in the trial [19].

This paper describes the design and baseline findings of a health promotion intervention targeting PA and healthy eating in people with MD living in sheltered housing, whereby the above mentioned design issues were accounted for. Our design is innovative in a way that preference occurred at the level of the sheltered housing organisation (SHO) and not on the level of the individual patients. The description of the study protocol is in agreement with the checklist of the CONSORT statement for cluster randomized trials [20].

## Methods and design

### Aim of the study and hypotheses

The aim of the study is to evaluate the effectiveness and cost-effectiveness of a health promotion intervention targeting PA and healthy eating in people with MD living in sheltered housing. We hypothesize that:

· Between baseline and the end of the intervention and after a 6-month follow up period, significant differences in the primary outcomes ‘body weight’,‘Body Mass Index’ (BMI), ‘waist circumference’ (WC), ‘fat mass’ between the intervention and control group will be identified;

· Between baseline and the end of the intervention and after a 6-month follow up period, significant differences in the secondary outcomes ‘quality of life’ (QOL), ‘PA levels’, ‘eating habits’, and ‘psychiatric symptom severity’ between the intervention and the control group will be identified;

· The health promotion intervention is cost-effective.

### Study design and setting

The design consisted of a cluster preference randomized controlled trial. An overview of the study design can be found in Figure 1. The study was conducted in sheltered housing organisations (SHOs) in the Flanders region (Belgium) with the SHOs as the unit of randomization. In SHOs, support on several domains (e.g. psychological, domestically, occupational, relational) is offered to the patients. In this type of health care service, patients are living alone in a studio or apartment or together with other patients in ‘community houses’. For this reason, cluster randomization was appropriate. Individual randomization at the level of the individual patient would decisively cause contamination bias due to the risk of participants in the intervention and control group living together. Cluster randomization to the intervention or control group therefore occurred at the level of the SHOs.

**Figure 1 F1:**
[figure not shown]
Health promotion intervention: Study design.

Mental health professionals working in the intervention SHOs were asked to lead and to support the health promotion intervention. This implied a significant involvement and workload above their usual workload. Also, as mentioned before, centers being assigned to a non-preferred intervention arm could be disappointed, which may reduce their interest to participate in the study [12,13]. Moreover, a substantial risk of non-participation was also assumed based on the results of previous qualitative research indicating that lack of time due to the high workload in the daily care of patients is a common barrier for mental health professionals to engage in health promotion programs [21,22]. Consequently, it appeared to be necessary to provide a detailed explanation about the expectations when serving as an intervention SHO. For this reason, preference randomization appears to be appropriate.

An invitation letter and response form with a self-addressed postage envelope was sent to the managers of all SHOs in the Flanders region. They were asked if they were interested to participate in the study having (i) no preference to serve as intervention or control group and to be randomized or, (ii) a preference to serve as intervention group (see a detailed description of the intervention below) or, (iii) a preference to serve as control group. A concise explanation of the aim of the study and of the expectations and content when participating as intervention group was included in the letter. If necessary, a second mailing was foreseen. If a SHO was not prepared to participate, they were asked to report the reason for non-participation.

Subsequently, based on the responses, SHOs were either assigned to the intervention or control group according to their preference or randomly assigned to the intervention or control group when they expressed no preference. Randomization occurred by an external person not involved in the study. Finally, the patients living in the intervention and control SHOs received both written and oral information about the study. The written information consisted of a detailed explanation about the study and an informed consent.

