### Study duration and intervention components

The study period consists of an intervention period of 10 weeks followed by a post-intervention period of six months. In addition to treatment as usual, the intervention groups (n = 14) receive the 10-week health promotion program targeting PA and healthy eating. In the intervention group the following intervention components are offered:

· Psycho-educational and behavioral group sessions

This part of the program consists of 10 group sessions in a 10-week period and includes discussions on PA and healthy eating, problem solving, written exercises, quizzes and plans to increase PA levels and to stimulate a more healthy eating behavior. All participants in the intervention group receive the same information in the same format. The program is delivered by the mental health professionals working in the intervention SHOs.

· Supervised exercise

In the same 10-weeks period a weekly 30-minutes supervised walking session is organized. These sessions are also led by one or more mental health professionals.

· Individual counseling

During the 10-week intervention period, all participants in the intervention group receive individual support from the mental health professionals (for example motivation to persist, discussing of experiences).

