### Data analysis

Parametric and non-parametric tests are used at the individual level to compare the intervention and control group at baseline, depending on the distributions of the quantitative variables. The X²-test is used in qualitative variables. Repeated measure analyses will be used to evaluate differences in the primary outcome variables body weight, BMI, WC and fat mass between pre- and post-intervention in the intervention and control group. Because preference randomization occurred at the level of SHO and not at the level of the individual patient, cluster effects will also be examined. The analyses of the primary outcomes will be performed on an intention to treat (ITT) basis. Secondary outcome variables will be evaluated per protocol. A P-value ≤0.05 is considered statistically significant. For statistical analyses, SPSS®19 will be used.

To examine the cost-effectiveness of the intervention, a Markov decision-analytic model assuming a public payer perspective will be constructed to project health outcomes and costs of the health promotion intervention compared with usual care. Overweight and obesity are substantial risk factors for the high prevalence of type 2 diabetes and cardiovascular disease in individuals with MD[35,36]. Therefore, the Markov model will be used to estimate, for both the intervention and control group, the development of cardiovascular disease and type 2 diabetes over time and the associated costs. The time horizon will be a 10-year period. In both the intervention and control arm several health states will be included in the Markov model. All future costs and health outcomes will be discounted respectively at 3% and 1.5% annually. The costs will be calculated by analyzing the direct health care costs and the costs of the program. The direct health care costs include hospitalization, medication, GP consultations, and other health professionals costs. The program related resource use (staff time, materials) and resulting costs will be calculated making a distinction between the resource used and costs related to the research purpose and those related to the intervention itself.

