## Baseline study population characteristics

A schematic overview of the recruitment process is shown in Figure 3. Twenty-five SHOs were interested to participate. Fourteen of these expressed a preference to serve as intervention group, while five preferred to serve as control group. Six expressed no preference neither for the intervention nor for the control group. These six were randomly assigned to the intervention group (n = 2) and to the control group (n = 4). In one of the SHOs serving as controls no patients were interested to participate.

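### Nineteen of the 25 sheltered housing organisations (SHOs) chose their arm, so the main contrast is largely non-randomised, and examining cluster effects does not deal with that

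*Protocol article*

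**What the plan says.** Under Study design and setting, the protocol article describes a cluster preference randomised controlled trial, names the SHO as the unit that was randomised, and says that cluster randomisation took place at SHO level. The text after Figure 1 gives the actual rule: "SHOs were either assigned to the intervention or control group according to their preference or randomly assigned to the intervention or control group", with randomisation kept for SHOs that stated no preference. Patients are informed and asked for consent as the last step, once their SHO belongs to a group.

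Baseline study population characteristics puts the number of SHOs at 25 and breaks it down as follows: "Fourteen of these expressed a preference to serve as intervention group, while five preferred to serve as control group". The other six had no preference, of which two were randomised to intervention and four to control. It adds that "In one of the SHOs serving as controls no patients were interested to participate".

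The hypotheses are framed as differences between the intervention and the control group. Under Data analysis, "Repeated measure analyses will be used to evaluate differences in the primary outcome variables" between the two groups, by intention to treat. The one provision linked to preference allocation is that cluster effects will be examined as well. Tables 1 and 2 show two groups (201 and 83 patients) and are not split by how the SHO was allocated.

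Study duration and intervention components says that "the intervention groups (n = 14) receive the 10-week health promotion program".

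**The concern.** When a cluster picks its own arm, whatever led to the choice travels with the treatment. The article itself gives grounds for thinking that the choice is not neutral. It justifies the preference design by the extra work asked of staff, and points to previous research on taking part in such programmes: "lack of time due to the high workload in the daily care of patients is a common barrier for mental health professionals". The same professionals deliver the sessions and the counselling. SHOs with more time for this work may differ from the others in the care that their residents receive with or without the programme.

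Because patients consented after their SHO had been allocated, selection of individuals can add to selection of SHOs.

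Examining cluster effects corrects the standard error for correlation among residents of one SHO. It leaves the point estimate exposed to selection. If the plan is followed as written, a difference in weight change could reflect which SHOs volunteered, yet be reported under the label of a randomised trial. The cost-effectiveness comparison of the programme with usual care would rest on the same contrast.

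**Working it through.** **1. Counts (Baseline study population characteristics).**
- All SHOs: 14 + 5 + 6 = 25, which reproduces the stated total.
- Chose their arm: 14 + 5 = 19; 19/25 = 76%. Randomised: 6/25 = 24%.
- Intervention arm: 14 + 2 = 16 SHOs, of which 14/16 = 87.5% chose it.
- Control arm: 5 + 4 = 9 SHOs, of which 5/9 = 55.6% chose it.
- One control SHO had no participants, so at most 24 SHOs contribute data. The article does not say whether that SHO was a preference or a randomised one.

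**2. Alignment of preference with arm.** A preference for intervention is present in 14/16 intervention SHOs and 0/9 control SHOs. A preference for control is present in 0/16 and 5/9. Within the 19 preference SHOs, preference and arm are the same variable.

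**3. Measured imbalances (Table 1 and the text after Table 2).**
- Living with others: 62% intervention, 81% control (p < .05).
- Median stay in sheltered housing: 4.4 versus 2.5 years (p < .05).
- Antipsychotics as the only class: 26.1% versus 14.3% (p = .05).

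The medication rows are mutually exclusive. They sum to 3+46+8+31+16+9+58+5 = 176 in the intervention group and 4+10+4+18+4+7+17+6 = 70 in the control group. Adding the four rows that contain an antipsychotic:
- Intervention: 46+31+16+58 = 151; 151/176 = 85.8%.
- Control: 10+18+4+17 = 49; 49/70 = 70.0%.
- Chi-square = 246 × (151×21 − 25×49)² / (176×70×200×46) = 8.2, p about 0.004. This ignores clustering, so the p-value is too small; the 15.8-point difference is the relevant figure.

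The Background links atypical antipsychotics to body weight, which is a primary outcome.

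**4. Possible size of the bias (illustration, not a figure from the article).** Suppose SHOs that prefer intervention would differ from all others by b kg in weight change whatever the programme does, and SHOs have equal weight. The contrast is then biased by b × (14/16 − 0/9) = 0.875b:
- b = 0.5 kg: 0.44 kg
- b = 1 kg: 0.88 kg
- b = 2 kg: 1.75 kg

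The target difference under Sample size calculation is 3.5 kg. The article gives no value for b, and its sign is unknown.

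**5. What the randomised SHOs can carry.** Given a 2 versus 4 split there are C(6,2) = 15 possible allocations, so the smallest exact randomisation p-value is 1/15 = 0.067. If the empty control SHO was a randomised one, the split is 2 versus 3, C(5,2) = 10, and the minimum is 1/10 = 0.10. Neither can reach 0.05. The plan proposes no such test; the figures show only that this stratum can be described and not tested.

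**6. Number of intervention units.** Study duration and intervention components gives 14; the recruitment figures give 14 + 2 = 16.

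**The case against.** The strongest reply is that the preference design is open and reasoned. It is named in the abstract and the methods, the grounds for it are given, and the numbers who chose and who were randomised are reported. Covariate lists and model terms commonly sit in a full protocol or SAP, so their absence from a journal article shows nothing. A repeated-measures analysis of change already removes fixed differences in level, so only a differing weight trend can bias it. Response rates were similar (24% and 21.1%).

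Much of this stands. A reader might infer that the authors conceal the self-selection, or that the plan rules out adjustment. Neither is supported: the design is disclosed, and Data analysis excludes no covariate. A reader might also take the non-significant baseline weights as offered in reassurance, or staff motivation as a stated reason for preference. The article only reports the p-values, alongside the variables that do differ, and it names workload, lack of time and disappointment.

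What does not fall away is that the self-selection is fixed by the allocation, whatever an SAP adds. The article still says that SHOs were cluster-randomised, and its one stated response to preference allocation does not address selection. Similar response rates do not show that similar residents responded, and equal baseline weight does not show equal expected trends.

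**Conclusion.** The point holds. For 19 of 25 SHOs (76%) the arm was chosen, so the intervention-control contrast is a largely non-randomised comparison confounded with SHO preference. That conclusion rests only on the article's own counts. The size of any bias is unknown; 0.875b is an illustration under equal SHO weights and an assumed b.

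Two stronger readings should be avoided. First, a term for allocation mode (preference versus randomised) might seem to remove the confounding. It cannot, because preference and arm coincide in all 19 preference SHOs. Second, the figure of 14 intervention groups might suggest that the two SHOs randomised to intervention went untreated. The article does not say which units the 14 are, so this is only a discrepancy to be reconciled.

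**What to change.** 1. Describe the overall estimate, and the effectiveness and cost-effectiveness conclusions that rest on it, as a largely non-randomised comparison. Correct the statement that SHOs were cluster-randomised so that it applies to the six that were. This is the essential change.
2. In the primary clustered repeated-measures model, adjust for prespecified baseline covariates already collected: sex, age, living situation, length of stay, diagnosis and any antipsychotic use. They should act on change (covariate-by-time terms if the baseline measurement is kept as a repeated outcome). State that this reduces measured confounding only.
3. Report the arm effect separately for preference and randomised SHOs, as description without a test. If allocation mode enters a model, do not present it as removing the confounding.
4. Separately, reconcile the 14 intervention groups with the 16 SHOs assigned to intervention, and analyse all SHOs as assigned.

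No new data are needed. The costs are a weaker causal claim, possibly a slightly wider interval, and a need to handle incomplete covariates: Table 1 has medication data for 176 of 201 and 70 of 83 patients.

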### Study population

The study population consisted of people with MD aged between 18 and 75 years living in a SHO in the Flanders region (Belgium). There are 42 SHOs in the Flanders region, including 2662 approved places [23]. Exclusion criteria included people aged <18 or older than 75 years, having a gastric ring or pacemaker placed, having cognitive impairments (assessed by the mental health professionals) compromising the understanding of the psycho-educational and behavioral sessions of the health promotion intervention.

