**Figure 3 F3:**
[figure not shown]
Health promotion intervention: Recruitment process.

On the individual level 324 patients were willing to participate, including 225 and 99 candidates in respectively the intervention and control SHOs. This accounted for a response rate of 24% in the intervention group and 21.1% in the control group. Eleven respondents were excluded because of age (n = 2), cognitive impairments (n = 4), having a gastric ring placed (n = 1), and the impossibility to be weighed using the digital weighing scale (n = 4). Of these four patients, three had a pacemaker and one patient had an artificial limb. Twenty-nine (9.3%) of the remaining 313 candidates withdrew before the baseline measurement due to hospital admission (n = 4), no further interest (n = 24), and one patient died in the period prior to the baseline measurement. This resulted in 284 patients for whom baseline data are available.

The sociodemographic characteristics for the overall study population and by treatment group are listed in Table 1. The overall study population consisted of 174 men (61.3%) and mean age at enrollment was 46.3 years. Two-thirds of the patients (67.7%) were living together. Sixty-one percent of the participants were daily smokers and 46% used alcohol on a regular basis. The most frequent psychiatric diagnosis consisted of schizophrenia (37.9%), followed by mood disorders (24.5%). Mean baseline body weight was 87.1 kg. Sixty point three percent of men had a baseline WC of >102 cm. In women, 86.4% had a WC of >88 cm. Of the total sample, 33.4% were classified as overweight and 47.2% as obese (Table 2).

**Table 1 T1:** Baseline sociodemographic data

**Variable**	**All (n = 284)**	**Intervention group (n = 201)**	**Control group (n = 83)**	***p***
Sex				.27§
men, *n (%)*	174 (61.3)	119 (59.2)	55 (66.3)	
women, *n (%)*	110 (38.7)	82 (40.8)	28 (33.7)	
Age (years), *mean ± SD*	46.3 ± 12.3	46.2 ± 12.5	46.5 ± 11.9	.83‡
Smoking status, *n (%)*				.22§
no smoking	103 (39)	77 (41.4)	26 (33.3)	
smoking	161 (61)	109 (58.6)	52 (66.7)	
Alcohol use, *n (%)*				.81§
regular	122 (46)	87 (46.5)	35 (44.9)	
never	143 (54)	100 (53.5)	43 (55.1)	
Employment, *n (%)*				.51§
regular	13 (4.9)	11 (5.9)	2 (2.5)	
sheltered	105 (39.6)	73 (39.2)	32 (40.5)	
no	147 (55.5)	102 (54.8)	45 (57.0)	
Living situation, *n (%)*				<.05§
alone	86 (32.3)	71 (38)	15 (19)	
with others	180 (67.7)	116 (62)	64 (81)	

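### Patients were recruited after their SHO's arm was assigned, so who entered can differ by arm even in the six randomised SHOs; adjust for a covariate set fixed in advance and limit the conclusion

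*Protocol article*

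**What the plan says.** The order of steps is in the protocol article under Study design and setting. Once managers had replied, "SHOs were either assigned to the intervention or control group according to their preference or randomly assigned to the intervention or control group", the latter when they had no preference. The next step is described as "Finally, the patients living in the intervention and control SHOs received both written and oral information about the study". On the consent material it says: "The written information consisted of a detailed explanation about the study and an informed consent". The one safeguard described is "Randomization occurred by an external person not involved in the study". No other order is given for the SHOs that were randomised.

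Study population excludes people "having cognitive impairments (assessed by the mental health professionals) compromising the understanding of the psycho-educational and behavioral sessions of the health promotion intervention".

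Baseline study population characteristics reports the losses that followed. At SHO level: "In one of the SHOs serving as controls no patients were interested to participate". At patient level, after 11 exclusions from 324 candidates, "Twenty-nine (9.3%) of the remaining 313 candidates withdrew before the baseline measurement", which left 284 with baseline data.

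The primary outcomes are changes in weight, BMI, waist circumference and fat mass. Under Data analysis: "The analyses of the primary outcomes will be performed on an intention to treat (ITT) basis". The article does not say which people form that set.

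**The concern.** In a cluster trial, randomising the clusters makes individuals comparable only if the people who enter each cluster are identified without regard to its arm. Here they entered afterwards. Residents of intervention SHOs were being asked to join ten group sessions, weekly supervised walks and individual counselling. Residents of control SHOs were being asked for measurements and questionnaires on top of usual care. The two offers may attract different people.

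The article itself treats motivation as a mediator of behaviour change (Development of the materials) and names poor motivation as a barrier to engagement (Discussion), so motivation at entry is plausibly prognostic for weight. The cognitive exclusion adds a second route. It is a judgement by mental health professionals, is worded around sessions that only one arm receives, and in intervention SHOs such staff also deliver the programme.

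This is separate from SHO preference. Restricting the analysis to the six randomised SHOs would remove the preference problem and leave this one. If entry did differ, the contrast in weight and the other primary outcomes would mix the effect of the programme with the type of volunteer.

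**Working it through.** **1. Participant flow** (Baseline study population characteristics; Tables 1 and 2).
- Exclusions: 2 + 4 + 1 + 4 = 11, and 324 − 11 = 313.
- Withdrawals before baseline: 4 + 24 + 1 = 29, and 29/313 = 9.3%, as stated.
- Baseline set: 313 − 29 = 284 = 201 + 83, as stated.

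The article's flow reproduces exactly.

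**2. Loss between agreeing and baseline, by arm** (by subtraction).
- Intervention: 225 − 201 = 24, and 24/225 = 10.7%.
- Control: 99 − 83 = 16, and 16/99 = 16.2%.
- Overall: 40/324 = 12.3%.
- Difference, control minus intervention: 5.5 percentage points, 95% CI −2.8 to 13.8; Fisher p = 0.20, chi-square p = 0.17. These ignore clustering, and allowing for it would normally widen the interval.

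The intervention-arm loss of 24 is not the same count as the 24 withdrawals for lack of interest, which are for both arms together.

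**3. Uptake.** The article does not define the denominator of its response rates. Assuming it is the number of residents approached:
- Intervention: 225/0.24 ≈ 938 (918 to 957, given rounding of 24%).
- Control: 99/0.211 ≈ 469 (468 to 470).
- Response 24% vs 21.1%: difference 2.9 points, p about 0.23, clustering ignored.
- Share reaching baseline: 201/938 = 21.4% vs 83/469 = 17.7%; overall 284/1407 = 20.2%.

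On that assumption about four in five did not enter. That leaves much room for selection, but it does not show that selection differed by arm.

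**4. How SHOs reached their arm.** 14 + 5 = 19 of 25 chose it; six were randomised, 2 to intervention and 4 to control. The article's text gives no patient counts for those six separately. Controls number 5 + 4 = 9 SHOs, one of which recruited nobody; whether it was randomised or chose its arm is not stated. No matching intervention figure is used here, because the number of intervention groups is 14 under Study duration and intervention components but 14 + 2 = 16 under Baseline study population characteristics.

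**5. Baseline comparison** (Tables 1 and 2, intervention vs control).
- Primary variables: weight p = .23, BMI p = .37, waist p = .65, fat mass p = .57.
- Living with others: 62% vs 81%.
- Median stay: 4.4 vs 2.5 years.
- Antipsychotics (Table 1 category): 26.1% vs 14.3%, p = .05.

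**6. Who can be in the primary analysis.** The outcomes are changes from baseline, and the 40 people lost before baseline have no baseline value. Unless something is imputed for them, the analysed set is at most the 284.

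**7. Covariate completeness** (summing Table 1 counts).
- Living situation: 86 + 180 = 266 of 284 (18 missing).
- Diagnosis: 105 + 68 + 44 + 40 + 20 = 277 (7 missing).
- Medication: 7 + 56 + 12 + 49 + 20 + 16 + 75 + 11 = 246 (38 missing).

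A complete-case analysis on these three would lose between 38 participants (full overlap) and 18 + 7 + 38 = 63 (no overlap), that is 13.4% to 22.2% of 284.

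**The case against.** The strongest reply is that no bias has been shown, and that stands. Response and pre-baseline loss do not clearly differ by arm, and the four primary variables were similar at baseline. The differences in living situation, length of stay and antipsychotic use may only reflect which SHOs chose which arm. Similar rates do not show that similar people entered, however, because selection acts on who joins as well as on how many.

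Four stronger readings are tempting, and the article does not support them:
- *Recruitment bias is present in the six randomised SHOs.* Nothing reported separates them from the other 19. That patients knew their arm before consenting is itself a strong inference from the order of steps, not a stated fact.
- *Four in five selected themselves out because of the allocation.* The denominator is an assumption. Low uptake that is similar in both arms mainly limits generalisability. Of the 40 lost after agreeing, 11 were excluded, 4 were admitted to hospital and 1 died.
- *The cognitive exclusion cannot be applied alike in both arms.* It is set for the whole study population, and staff can judge whether a control resident would follow such sessions. Unblinded judgement may be uneven, but only four people were excluded on this ground, with no arm given in the text.
- *The plan defines ITT as the 284.* It defines no set; an article may leave that to a fuller document, and those lost are called candidates.

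It may also be said that an article condenses. That does not meet the point, which rests on a sequence that the article states.

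**Conclusion.** The point holds as a design weakness, not as demonstrated bias. Allocation came before information, consent, screening and baseline measurement in every SHO. Individual-level selection can therefore differ by arm, including in the six randomised SHOs, and external randomisation of SHOs does not guard against it. The reported figures neither establish a difference nor exclude one: the interval for the difference in pre-baseline loss runs from −2.8 to 13.8 points before clustering is allowed for.

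The effect on the weight contrast cannot be sized from the article, because motivation is not among the baseline variables it lists and recruitment is not reported separately for the randomised SHOs. That the intention-to-treat analysis will in practice cover the 284 measured participants as allocated is a probable inference from the endpoint definition. Confidence is high on the order of steps and moderate on the analysed set. The plan should be changed on this point; no recalculated sample size or power follows from it.

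**What to change.** (a) **Adjust the primary comparison.** Before any outcome analysis, fix a covariate set chosen on prognostic grounds, not by baseline p-values, from data already collected: baseline value of the outcome, age, sex, diagnosis, living situation, length of stay and antipsychotic use. Adjust the repeated-measures comparison for it and account for clustering by SHO in the same model. Enter the baseline outcome either as a covariate or as the first repeated measure, not both. Define antipsychotic use explicitly, since Table 1 splits medication into combinations. State how missing covariates are handled, so that the 38 to 63 participants above are not dropped.

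(b) **Limit the conclusions.** State that patients were recruited after allocation, that adjustment cannot remove unmeasured motivation, and that individuals in the six randomised SHOs are not protected from selection.

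The cost is a little more analysis work on data already held and a more cautious conclusion. Adjustment reduces confounding by what was measured and no more. Completing consent, screening and baseline measurement before allocation is released is a lesson for a future trial only, since baseline is complete here.
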